### **11.3 Case Report Forms**

This study does not require the use of case report forms for research purposes.

### **11.4 Study Records Retention**

We will retain de-identified study records and the mastercode file 7 years after completion of the study, after which we will shred or permanently delete such documentation.

## **12 Statistical Plan**

### **12.1 Study Hypotheses**

We hypothesize THRIVE+ will increase connection to, and receipt of, resources to reduce the burden of HRSN, thereby reducing avoidable acute healthcare utilization, among intermediate risk BACO patients. This hypothesis is based on the evidence that the disproportionate utilization of the top 3-10% risk tier among BACO membership is driven in large part by social risk. We hypothesize that optimally addressing patients' HRSN will better positioned them to manage chronic conditions and adhere to preventive care plans, thereby reducing the likelihood they will use the emergency department or require inpatient care.

The null hypothesis is THRIVE+ does not reduce acute healthcare utilization (IP and ED visits) among intermediate risk BACO patients over the 12 month follow-up period.

The alternative hypothesis is THRIVE+ does reduce acute healthcare utilization (IP and ED) among intermediate risk BACO patients over the 12 month follow-up period.

### **12.2 Sample Size Determination**

*Sample Size.* We derived the sample size that is needed to detect an overall difference which is of clinical significance and with potential cost-saving implications. We have powered our study to detect the primary outcome (10% relative reduction in overall hospital admissions and overall ED visits) at 12 months. We estimate 1,500 BACO members are eligible intermediate risk patients. We know from existing institutional data that these intermediate risk BACO members experience an average of 4.3 inpatient admission over 12 months, and 10.2 ED visits over 12 months. With these baseline data, we estimate that a total sample size of 364 patients (N=182 in each arm) is adequate to detect a 10% reduction in total ED plus hospital visits with statistical power of 0.90 and two-sided type I error rate of 0.05, accounting for 80% retention over a 12-month study period.

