We will first examine descriptive statistics of all variables. For categorical variables, we will report proportions, and for continuous variables, we will report means, standard deviations, and ranges. We will assess the randomness of treatment assignment according to odd versus even patient medical record number by comparing patient characteristics by treatment status. In order to determine if the THRIVE+ condition achieves a greater reduction (or smaller increase) in all-cause hospital admissions and all-cause emergency department visits (our composite primary outcome) in the 12 months following enrollment compared to the THRIVE-Basic condition, we will compare groups on their average number of visits in the 12 months post-intervention period controlling for potential baseline differences and any covariates (e.g., age, gender) determined *a priori* as important predictors of healthcare utilization. We will note differences that are statistically significant at the  $\alpha < 0.05$  level. We will assess the distribution of the outcome variables, diagnose error terms in residual analysis, and use appropriate link functions (e.g., normal link function for continuous outcomes with normal distribution) to construct linear regression models to assess the treatment effect. We will further assess any potential collinearity among covariates by evaluating variance inflation factors and correlation matrices. The primary analyses will be based on intent-to-treat. Because participants may receive varying “doses” of the THRIVE+ intervention, we will also analyze the intervention effect according to whether participants received a “minimum dose” of the intervention. In order to assess whether the presence of comorbid mental health and substance use diagnoses, race, and language may modify the treatment effect, we will evaluate interaction terms between these pre-determined potential moderators and the treatment variable in the overall sample, and further conduct stratified analyses among these potential modifiers to assess the robustness of any differential effects if detected above.

We will report our results according to CONSORT guidelines.

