|  | 
categorical variables. Due to a potential high number of patients with zero-count visits (136 out of 364, 37%), we employ a zero-inflated negative binomial model, which is a two-part model that examines simultaneously the odds of any visit, and the rates of visits among those patients who have any health care utilization. We use Bayesian Information Criteria as the model goodness-of-fit measure to compare zero-inflated negative binomial model with other models for the rates outcomes, including over-dispersed Poisson model, and negative binomial model. As a sensitivity analysis, we also model only the binary outcome of any utilization using logit link function. In the adjusted regression models, we will control for any factors including baseline utilization that are found statistically significant between the two arms. We report odds ratios and 95% CI for binary outcome (e.g., any visit) and rate ratios for the outcomes of inpatient and ED visits. We also compare the secondary outcomes of health-related social needs (e.g., connected to community-based partner; received services through referral to community partner; referrals and visits to hospital food pantry; received utility shutoff protection letter) between the two arms and examine adjusted intervention effect using logistic regression with odds ratio and 95% CI.
 
The primary analyses will be based on intent-to-treat. Because participants may receive varying “doses” of the intervention, we will also analyze the intervention effect according to whether participants received a minimum dose of the intervention. If the pharmacy liaison-patient navigator documents in their first telephone assessment that the patient has received the THRIVE screening in the past three months, and rescreens the patient if they have not been screened in the past three months, we consider the patient to have received the minimum intervention dose.
 |

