### **3.3 Sample size**

We used internal health care utilization data from the institution for sample size calculation. Using a two-sided type-I error rate of 0.05, a sample size of 364 patients (N=182 in each arm) would achieve 90% power to detect a 10–percentage point reduction in our primary outcome of total emergency department visits plus inpatient hospital admissions.

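### The 90% power claim for a 10% reduction needs a near-Poisson spread of visits, which the SAP's own 37% of patients with no visits does not allow

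*Combined protocol and SAP*

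**What the plan says.** Protocol 12.2 sets the target as a "10% relative reduction in overall hospital admissions and overall ED visits" at 12 months. It takes from institutional data "an average of 4.3 inpatient admission over 12 months, and 10.2 ED visits over 12 months". Its conclusion is: "a total sample size of 364 patients (N=182 in each arm) is adequate to detect a 10% reduction in total ED plus hospital visits". The operating characteristics are stated as "statistical power of 0.90 and two-sided type I error rate of 0.05". The allowance for loss is worded as "accounting for 80% retention over a 12-month study period". No SD, dispersion or distribution is given.

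SAP 3.3 says of the same 182 per arm that it "would achieve 90% power to detect a 10–percentage point reduction in our primary outcome of total emergency department visits plus inpatient hospital admissions". It does not mention retention, and SAP 4.3 expects no missing outcome data.

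On analysis, protocol 12.3 says "we will compare groups on their average number of visits in the 12 months post-intervention period controlling for potential baseline differences", and SAP 5.3.2 keeps a comparison of average visits. The Statistical method row of the SAP synopsis states: "Due to a potential high number of patients with zero-count visits (136 out of 364, 37%), we employ a zero-inflated negative binomial model". That model has one part for having any visit and one for the rate of visits. The SAP does not revisit power for it.

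**The concern.** A sample size for a mean count depends on the variance, and here the variance can only be inferred. The one that returns 182 is a variance equal to the mean. A Poisson count with mean 14.5 would leave almost no patient without a visit, yet the SAP gives 37%. A population mixing many non-users with users averaging well above 14.5 varies far more than the stated power can tolerate.

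Protocol 12.2 ties the 10% target to clinical significance and cost saving. With 90% power on record, a reader could take a non-significant result as evidence against a 10% reduction, although the trial may have had little chance of detecting one.

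**Working it through.** **Inputs.** Mean 4.3 + 10.2 = 14.5; 10% reduction = 1.45; two-sided 0.05; power 0.90; 80% retention (protocol 12.2). Zero share p0 = 136/364 = 0.374 (SAP synopsis). Planning constant: 1.960 + 1.282 = 3.242, squared 10.51. Calculations use n = 145 per arm (evaluable after 80% retention) and n = 182 (no loss).

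**1. The plan's figure.** With variance equal to the mean, n = 2 × 14.5 × 10.51 / 1.45² = 144.9, so 145; 145/0.8 = 181.25, so 182. This is an exact match. Arm-specific Poisson variance, the log rate ratio and the square-root scale each give 138, or 173 after retention.

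**2. The SD that 90% power requires.** SD ≤ 1.45 / (3.242 × √(2/n)): 3.81 at n = 145 and 4.27 at n = 182.

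**3. What 37% zeros imply.** A Poisson with mean 14.5 expects 364 × e^(−14.5) ≈ 0.0002 patients with no visit. More generally, for mean m and zero share p0 the variance is at least m² × p0/(1 − p0), reached only if all users have the same count. So CV² ≥ 0.374/0.626 = 0.60 at any mean. At mean 14.5 the variance is at least 125.4 and the SD at least 11.2.

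**4. Best-case power, unadjusted means.** With the same zero share in both arms:
- Difference scale, z = 1.45 / (11.2 × √(2/n)): 1.10 at n = 145 and 1.24 at n = 182, so power 20% and 23%.
- Log scale, z = 0.105 / √(2 × 0.596/n): 1.16 and 1.30, so power 21% and 26%.
- Reduction detectable with 90% power: log scale, 1 − exp(−3.242 × √(2 × 0.596/n)) = 25% and 23%; difference scale, 3.242 × √(2 × 0.596/n) = 29% and 26%.

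**5. Plain negative binomial with the same zeros.** Solving (1 + m/k)^(−k) = 0.374 gives k = 0.511 at an assumed mean of 3 and 0.239 at 14.5. The variance of the log rate ratio is (1/m + 1/k + 1/(0.9m) + 1/k)/n. Counting both rejection tails, power runs from 7% (mean 14.5, n = 145) to 10% (mean 3, n = 182). Detectable reduction with 90% power on the log scale, using 2(1/m + 1/k)/n: 54% down to 40%. A simulation at mean 14.5 gave 6–7% for this model and 20–23% for a zero-inflated Poisson.

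**6. Baseline adjustment, assumed R² = 0.5.** The standard errors in step 4 shrink by √0.5. The ceiling becomes 34% (n = 145, difference scale) to 45% (n = 182, log scale). Reaching 90% in this best case at n = 182 needs R² ≈ 1 − (4.27/10.65)² = 0.84, where 10.65 averages the arm variances (SD 11.2 and 10.08).

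**7. Count part of the zero-inflated model alone.** Users' mean is 14.5/0.626 ≈ 23; users per arm are 0.626n = 91 and 114. With dispersion a, the variance of the log rate ratio is 2(1/23.15 + a)/users.

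| Assumed dispersion | Power, n = 145 | Power, n = 182 |
|---|---|---|
| 0.1 | 47% | 56% |
| 0.5 | 16% | 19% |

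For 90% power, 1/23.15 + a must not exceed (0.105/3.242)² × users/2, so a ≤ about 0.005 (n = 145) or 0.017 (n = 182). That is close to Poisson.

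**The case against.** Several points on the other side stand and limit the claim.

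- **Poisson is inferred.** Protocol 12.2 names no distribution. A reader might infer that 90% holds only under a pure Poisson; any residual SD up to 3.8–4.3 would do.
- **Two sources are combined.** The mean of 14.5 is institutional data before the trial; the 37% describes the 364 patients, and the sentence does not say which visits or period it covers. The CV² bound holds at any mean, but the SD of 11.2 and the users' mean of 23 use both sources. The documents do not show that the zeros were known at design, so no careless planning should be inferred.
- **The ceiling is for unadjusted means.** A reader might take 7–26% as the trial's actual power. The documents do not support that: protocol 12.3 adjusts for baseline differences and chosen predictors, and the SAP model separates any visit from the rate among users. Adjustment and the count part both give higher figures. But the SAP ties control for baseline utilization to a significant difference between arms, so that gain is not assured, and a count-part test is not a comparison of average visits.
- **Percentage points are not meaningless.** Both documents define the outcome in one place as a percentage change, where ten percentage points could have a sense. It does not fit the summed count in SAP 5.4. Read as any visit falling from 63% to 53%, 182 per arm gives about 49% power.
- **Omitting retention is not clearly an error**, since SAP 4.3 expects complete outcomes.
- **Recruitment is reported complete**, so overwriting the rationale with power computed from trial data would be post-hoc. That argues for keeping the design-stage figure, labelled as such; it does not support repeating an unqualified 90% beside the zeros.

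**Conclusion.** The unqualified 90% in protocol 12.2 and SAP 3.3 is incompatible with the SAP's own zero count for a comparison of mean visits. The conclusion rests on the 37% applying to the 12-month composite, with a similar share in each arm. On that footing the required SD of 3.8–4.3 compares with at least 11.2 at mean 14.5, and unadjusted power cannot exceed about 20–26%.

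The remaining figures depend on assumptions the documents do not settle: the negative binomial mean, the R-squared and the users' dispersion. No single value should be called the trial's power. Nor do the documents say that a null result will be read as excluding a 10% reduction; that is a risk of leaving the claim unqualified, not a stated plan.

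**What to change.** 1. Keep N=364. Keep the existing calculation in protocol 12.2, labelled as the design-stage assumption with variance equal to the mean.
2. Withdraw the unqualified 90% in protocol 12.2 and SAP 3.3. Add power under the planned model, pairing each figure with its assumption:
   - best-case ceiling, unadjusted: about 20–26%, detectable reduction about 23–25% (log rate ratio) or 26–29% (difference in means);
   - plain negative binomial, assumed mean 3 to 14.5: about 7–10%, detectable reduction about 40–54% (log rate ratio);
   - ceiling with baseline adjustment at R-squared 0.5: about 34–45%;
   - count part alone: about 47–56% at dispersion 0.1 and 16–19% at 0.5.
3. State which visits and period the 136 of 364 refers to.
4. Reconcile the percentage-point wording in SAP 3.3 with the relative reduction in protocol 12.2, for example as a rate ratio of 0.90.
5. Reconcile the 80% retention with SAP 4.3 by giving power at both 145 and 182 per arm.
6. Commit to interpreting a non-significant result from the confidence interval.

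The cost is a revision of protocol and SAP text and a less favourable stated power. No extra patients are needed.

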### **12.3 Statistical Methods**

*Study consort diagram.*

*Data Analysis Plan.* Our primary outcome is the percentage change in all-cause hospital admissions and all-cause emergency department visits (a composite outcome) in the 12 months following enrollment. Secondary outcomes include total number of all-cause ED visits; all-cause 30-day ED revisits rate; total number of all-cause discharges from IP; all-cause 30-day IP readmission rate. Intermediate measures will be measured by: number and proportion of patients to have identified HRSN; number and proportion of patients to receive referrals for their HRSN; number and proportion of patients to receive community-based services to meet their HRSN; connection to housing resources; connection to employment resources; connection to food; and patient-level average of Proportion of Days Covered (PDC) for pharmaceutical prescriptions.

We will also collect data on demographics (age, gender, race, ethnicity, and language), insurance coverage (proportion of days covered from claims data), and on potential confounding variables, such as medical comorbidity as measured by the Elixhauser score), mental health and substance use diagnoses, THRIVE screening results, and medication adherence over 12 months using a measure of proportion of days covered based on pharmacy claims data.

We will first examine descriptive statistics of all variables. For categorical variables, we will report proportions, and for continuous variables, we will report means, standard deviations, and ranges. We will assess the randomness of treatment assignment according to odd versus even patient medical record number by comparing patient characteristics by treatment status. In order to determine if the THRIVE+ condition achieves a greater reduction (or smaller increase) in all-cause hospital admissions and all-cause emergency department visits (our composite primary outcome) in the 12 months following enrollment compared to the THRIVE-Basic condition, we will compare groups on their average number of visits in the 12 months post-intervention period controlling for potential baseline differences and any covariates (e.g., age, gender) determined *a priori* as important predictors of healthcare utilization. We will note differences that are statistically significant at the  $\alpha < 0.05$  level. We will assess the distribution of the outcome variables, diagnose error terms in residual analysis, and use appropriate link functions (e.g., normal link function for continuous outcomes with normal distribution) to construct linear regression models to assess the treatment effect. We will further assess any potential collinearity among covariates by evaluating variance inflation factors and correlation matrices. The primary analyses will be based on intent-to-treat. Because participants may receive varying “doses” of the THRIVE+ intervention, we will also analyze the intervention effect according to whether participants received a “minimum dose” of the intervention. In order to assess whether the presence of comorbid mental health and substance use diagnoses, race, and language may modify the treatment effect, we will evaluate interaction terms between these pre-determined potential moderators and the treatment variable in the overall sample, and further conduct stratified analyses among these potential modifiers to assess the robustness of any differential effects if detected above.

We will report our results according to CONSORT guidelines.

*De-identified data for inclusion in consort diagram.* We will review de-identified to develop our consort flow diagram depicting the process through which patients were approached, recruited, enrolled into the clinical program, and attributed to each of the two study comparison groups. Specifically, we will explore reasons for drop-off between patients approached for enrollment in the clinical program and patients who were ultimately attributed to the trial. We will review de-identified data for patients who drop-off: (1) BMC pharmacy intervention provider name (which indicates study arm) and (2) the reason for not being enrolled in clinical program. These are source data collected by clinical Pharmacy programs in the course of routine care within the program's client tracking system.

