#### 4.2.2 Secondary Outcome Measures

Secondary outcomes measures will be measured by:

1. Total number of all-cause ED visits;
2. Total number of all-cause 30-day ED revisits;
3. All-cause 30-day ED revisits rate;
4. Total number of all-cause discharges from IP;
5. Total number of all-cause 30-day IP readmissions;
6. All-cause 30-day IP readmission rate.

Intermediate measures will be measured by:

1. Number and proportion of patients to have identified HRSN;
2. Number and proportion of patients to receive referrals for their HRSN;
3. Number and proportion of patients to receive community-based services to meet their HRSN;
4. Connection to housing resources;
5. Connection to employment resources;
6. Connection to food;
7. Patient-level average of Proportion of Days Covered (PDC) for pharmaceutical prescriptions.

A budget impact analysis will be conducted to estimate the short-term expenditure changes and financial consequences of THRIVE+ compared to THRIVE-Basic, focusing on direct costs of implementation (staffing, resources, eligible intervention population size, etc.).

Post-hoc measures:

1. Social determinants of health services or referrals (e.g., food pantry referrals, food pantry visits, utilities shut-off protection letters).

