#### **Research Follow-Up Procedures – THIS IS PART 2 OF THE RESEARCH PROVISIONS**

We will assess outcome measures monthly for patients assigned to the THRIVE+ intervention arm, in order to satisfy a requirement of our funder. We will assess all outcome measures for all study participants at 6 months post-enrollment in the clinical program – again, to satisfy a requirement of our funder – and at 12 months post-enrollment in the clinical program.

As part of the research provisions, pharmacy liaisons-patient navigators will systematically screen patients assigned to the intervention arm with the THRIVE screener every three months to assess for new or unmet HRSN. These re-screens will take place during the monthly follow-up touches that are part of the existing clinical program.

We will analyze data collected via routine clinical care to ascertain primary and secondary study outcomes. There are three data sources for data collected as part of routine care:

1. BMC Clinical Data Warehouse
2. BMC HealthNet Claims Data
3. Pharmacy Care Program client tracking system

In addition, we will analyze data collected for research purposes. There is one data source for data collected for research purposes outside of routine clinical care:

1. Connection to resources at Action for Boston Community Development (ABCD), Inc.

To assess receipt of services our community partner for this study, ABCD, will check how many of the intervention arm study participants used services at ABCD to help address HRSN. ABCD will provide BMC with data to confirm patient receipt of services, the type of service received, and the date of receipt.

A Pharmacy Liaison-Patient Navigation Intervention to Reduce Inpatient and Emergency Department Utilization among Primary Care Patients in a Medicaid Accountable Care Organization: A Pragmatic Trial  
Version 1.3, August 5, 2021

611 Table 1. Study Outcomes

| Outcome measure                                                                    | Data Source                                                       | Data collected as part of Routine Care or for Research? | Measurement Time Points (Post-Enrollment)                                                                                                                                              |

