| Patients to receive services to meet their HRSN     | Action for Boston Community Development data                                                                                                       | Research     | Quarterly – All enrolled patients                                                                                                                                                      |
| Connection to housing resources                     | Action for Boston Community Development data                                                                                                       | Research     | Quarterly – All enrolled patients                                                                                                                                                      |
| Connection to employment resources                  | Action for Boston Community Development data                                                                                                       | Research     | Quarterly – All enrolled patients                                                                                                                                                      |
| Connection to food                                  | Action for Boston Community Development data                                                                                                       | Research     | Quarterly – All enrolled patients                                                                                                                                                      |
| Patient-level average of Proportion of Days Covered | BMC HealthNet Plan claims data                                                                                                                     | Routine Care | Quarterly – All enrolled patients                                                                                                                                                      |

|                                        |  |  |  |
|----------------------------------------|--|--|--|
| (PDC) for pharmaceutical prescriptions |  |  |  |
|----------------------------------------|--|--|--|

Table 2. Post-Hoc Measures

| Post-hoc measure                                     | Data Source                 | Data collected as part of Routine Care or for Research? | Measurement Time Points (Post-Enrollment) |

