| Duration of follow-up | 12 months                                                                                                                                                                                                                                                                                                                                                                                                                                                                                                                                                                                                                                                                                                                                                                                                                                                                                                                                                                                                                                                                                                     |
| Criteria for efficacy | 
Measures:
We collect data on demographics (age, gender, race, ethnicity, and language), insurance coverage (proportion of days covered from claims data), and on potential confounding variables, such as medical comorbidity as measured by a validated comorbidity index (the Charlson Comorbidity Score), mental health and substance use diagnoses, health-related social needs screening results, and medication adherence using a measure of proportion of days covered based on pharmacy claims data.
 
Primary end points:
Our primary outcome is the percentage change in all-cause hospital admissions and all-cause emergency department visits (a composite outcome) in the 12 months following enrollment.
 
Secondary end points:
Secondary outcomes include all-cause hospital admissions and all-cause emergency department visits as separate outcomes, all-cause 30-day hospital readmissions, 30-day ED revisit rates, and connection to resources (referral to food pantry, visits to food pantry, utility shutoff protection letters).
 |

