## **5. Primary outcome analysis**

### **5.1 Definitions**

Our primary outcome is all-cause hospital admissions and all-cause emergency department visits (a composite outcome) in the 12 months following enrollment. We compare baseline characteristics of participants using two-sample t tests for continuous variables or Chi-square tests for categorical variables. We assess the distribution of the outcome variables, diagnose error terms in residual analysis, and use appropriate link functions (e.g., normal link function for continuous outcomes with normal distribution) to construct linear regression models to assess the treatment effect. We will further assess any potential collinearity among covariates by evaluating variance inflation factors and correlation matrices. In the case where there are excess zeros (e.g., no visits), we employ a zero-inflated negative binomial model, which is a two-part model that examines simultaneously the odds of any visit, and the rates of visits among those patients who had any health care utilization. In the adjusted regression models, we will control for any factors including baseline utilization that are found statistically significant between the two arms.

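### Medication adherence and THRIVE screening results are undated confounders, and the SAP adjustment rule does not exclude their post-enrolment values from the primary model

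*Combined protocol and SAP*

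**What the plan says.** Protocol 12.3 gives one measure two roles in consecutive paragraphs. The first lists, among the intermediate measures, "patient-level average of Proportion of Days Covered (PDC) for pharmaceutical prescriptions"; section 4.2.2 has the same entry. The second announces data on demographics, insurance coverage "and on potential confounding variables, such as medical comorbidity". Its further examples include THRIVE screening results and "medication adherence over 12 months using a measure of proportion of days covered based on pharmacy claims data". Those 12 months are not labelled as before or after enrolment.

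The SAP synopsis (Criteria for efficacy, Measures) repeats the confounder list, including "health-related social needs screening results, and medication adherence using a measure of proportion of days covered", and gives no time window.

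The only PDC with a schedule is the outcome. Protocol Table 1 sets "Patient-level average of Proportion of Days Covered" quarterly for all enrolled patients, in a column of post-enrolment time points, from health plan claims. The schedule of events marks claims data at 6 and 12 months, monthly and quarterly, with no mark at screening or baseline.

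On adjustment, protocol 12.3 controls for baseline differences and for covariates chosen in advance, with age and gender as examples. SAP 5.1 says "we will control for any factors including baseline utilization that are found statistically significant between the two arms". The synopsis (Statistical method) has the same sentence, and SAP 5.3.2 has nearly the same.

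On screening, protocol sections 8 and 9 have navigators re-administer THRIVE every three months in the intervention arm. Control liaisons do not screen systematically (protocol section 8; SAP synopsis).

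**The concern.** A confounder must precede assignment. Adherence and screening results recorded after enrolment can be changed by the intervention, and the protocol itself treats both PDC and identified needs as intermediate outcomes. If such values enter the effect model, the estimate is no longer the total effect that an intent-to-treat analysis targets. Any part of the effect that runs through adherence is removed. Adjustment can also add bias through unmeasured causes shared by adherence and hospital use.

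The SAP rule provides a route for this. It selects covariates by a between-arm significance test, and it names baseline utilization as one included item, not as the limit. A real effect on PDC makes PDC more likely to be selected.

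Screening results have a further problem. After enrolment they are ascertained more often in the intervention arm, so the arms can differ in recorded needs when true needs are the same.

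**Working it through.** **1. The texts side by side**

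| Item | Protocol | SAP |
|---|---|---|
| PDC as outcome | Yes, quarterly after enrolment (4.2.2, Table 1, 12.3) | Not listed as an endpoint |
| Adherence as confounder | Yes, over 12 months, side of enrolment not stated (12.3) | Yes, no window (synopsis) |
| Screening results as confounder | Yes, undated (12.3) | Yes, undated (synopsis) |
| Adjustment rule | Baseline differences and a priori covariates (12.3) | Any factor significant between arms (synopsis, 5.1, 5.3.2) |
| Exclusion of post-enrolment values | None | None |

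SAP 5.3.2 contains both adjustment rules in one paragraph.

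**2. The plan's design figure, for scale**

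Protocol 12.2 gives 4.3 + 10.2 = 14.5 visits per year, a 10% reduction (1.45 visits), two-sided 0.05, power 0.90 and 80% retention. It states no SD. Assuming a Poisson SD, √14.5 = 3.81:

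n = 2 × (1.960 + 1.282)² × 14.5 / 1.45² = 145 per arm; 145 / 0.80 = 181.25, rounded up to 182 per arm, or 364 in total. This matches the protocol.

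**3. Size of the distortion if post-enrolment PDC is adjusted for**

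Let s be the share of the log effect that runs through PDC. The adjusted rate ratio is 0.90^(1−s). Power uses the 145 evaluable patients per arm and the same SD, with standard error 3.81 × √(2/145) = 0.447.

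| s (assumed) | Adjusted rate ratio | Nominal power |
|---|---|---|
| 0 | 0.900 | 0.90 |
| 25% | 0.924 | 0.69 |
| 50% | 0.949 | 0.38 |
| 75% | 0.974 | 0.13 |
| 100% | 1.000 | 0.025 |

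Example for 50%: 14.5 × (1 − 0.9487) = 0.744; 0.744 / 0.447 = 1.66; Φ(1.66 − 1.96) = 0.38. With PDC left out, the expected rate ratio stays at 0.90 whatever s is.

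**4. How often the rule would select PDC**

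Two-sided 0.05 test, 182 per arm, standard error SD × √(2/182). The documents give neither an SD nor an expected difference for PDC, so both are assumed.

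| True PDC difference | SD 0.20 | SD 0.25 | SD 0.30 |
|---|---|---|---|
| 0 | 5% | 5% | 5% |
| 0.03 | 30% | 21% | 16% |
| 0.05 | 67% | 48% | 36% |
| 0.10 | 99.8% | 97% | 89% |

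**5. Steps 3 and 4 combined**

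A simulation used 600 trials per scenario, a true total rate ratio of 0.90, PDC SD 0.25, 182 per arm and scaled Poisson regression, with the rule applied to post-enrolment PDC.

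- PDC difference 0.10: PDC was selected in about 97% of trials. The mean rate ratio was 0.924, 0.949 and 0.999 for 25%, 50% and 100% mediation. Power fell from 0.94 to 0.79, from 0.90 to 0.41 and from 0.78 to 0.06.
- PDC difference 0.05: PDC was selected in about half of trials. The mean rate ratio was 0.916, 0.933 and 0.971.

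No comparable figure can be given for screening results. More screening can find more need without changing visits, so the direction of bias is not fixed.

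**The case against.** The strongest reply is that the rule is meant for baseline variables. In the synopsis and in SAP 5.1, the passage containing the rule opens with a comparison of baseline characteristics, and 5.3.2 speaks of baseline differences. SAP 4.2 reports 12-month look-backs, such as food pantry use and screening in the past year, as characteristics at inclusion, so a look-back meaning for adherence is plausible. Routine THRIVE screening at check-in means that pre-assignment results exist. The double role of PDC is in the protocol only: the SAP drops the 12-month phrase and does not list PDC as an endpoint. Both arms receive the same adherence service, so a large PDC difference is not the expected result.

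Much of this stands. A reader might infer that the plan instructs the analyst to adjust for on-study adherence. It does not; it fails to exclude it. A reader might also infer that adjustment happens exactly when the intervention works. That is too strong: the rule selects PDC in about 5% of trials with no true difference, misses many modest differences, and a PDC difference is not the same as fewer visits.

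The reply does not remove the ambiguity. No section defines a pre-enrolment PDC, SAP 4.2 does not mention adherence, and the rule is worded for any factor. A careful analyst could apply only baseline values, but the text does not require it.

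**Conclusion.** The point holds as a fault of specification. Two covariates that can be consequences of assignment are undated, one of them is also a scheduled outcome, and the SAP rule does not keep their later values out of the primary model. The choice could therefore be made after the data are seen.

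If post-enrolment PDC entered the model, a true rate ratio of 0.90 would move to 0.924 at 25% mediation and 0.949 at 50%. The shares are assumptions. The power figures also rest on the Poisson variance that reproduces 364, and on a single log-rate effect rather than the SAP's two-part model, so they show scale only. Complete loss of the effect needs full mediation, which nothing in the documents supports: the hypothesis in protocol 12.1 runs through resources, chronic-condition management and preventive care plans, and does not name medication adherence. Nor should a reader conclude that needs met would be adjusted away; the confounder lists contain screening results, not receipt of services.

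The wording should be corrected. The documents do not show that the primary result is biased.

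**What to change.** In protocol 12.3 and in the SAP synopsis, 5.1 and 5.3.2, replace selection by between-arm significance test with one adjustment set named in advance and measured on or before enrolment: baseline utilization, PDC in the 12 months before enrolment, the last THRIVE screen before enrolment, and pre-enrolment comorbidity and diagnoses, together with the demographic covariates already intended. Dating the variables alone is not enough, because a significance rule would still let the data choose the model.

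State that post-enrolment PDC and health-related social needs are analysed only as outcomes or in a separate, labelled mediation analysis. Days of insurance coverage after enrolment may still serve as exposure time in the rate model.

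The cost is wording plus a look-back extraction of pre-enrolment pharmacy claims, with a rule for members whose prior coverage is shorter than 12 months. The claims source is already in use for the PDC outcome, so no new data source is needed.
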